# 3. PARTICIPANTS

## 3.1. Study population

Working men and women with subthreshold depression will be selected according to the following criteria:

### 3.1.1. Inclusion criteria

1. Age 20-60 at study entry
2. Men and women
3. Currently employed full-time by the business company
4. K6 scores greater than or equal to 5 at screening (while a sub-analysis will be done for all subjects including those with K6 scores of 0-4, as well)
5. Can access the Internet via a PC at home or at workplace

### 3.1.2. Exclusion criteria

1. Non-regular or part-time employees.
2. Sick leave for 15 or more days for a physical or mental condition in the past 3 months.
3. Current treatment for a mental health problem from a mental health professional.
4. Having major depressive episode in the past a month, as ascertained by the web-version of the Japanese WHO-CIDI 3.0.
5. Having lifetime history of bipolar disorder, as ascertained by the web-version of the Japanese WHO-CIDI 3.0.

All workers in company A (N=290) and all workers who belonged to three selected departments (N=about 1,500) at the headquarter of company B (the total employee size, c.a. 11,000) will be recruited by an invitation e-mail.

## 3.2. Sample size assumptions and estimates

A systematic review of psychological treatments, mostly CBT, for subthreshold depression yielded a Cohen’s d of 0.42 (95%CI: 0.23 to 0.60) at post-test ([Cuijpers, Smit, & van Straten, 2007](#_ENREF_8)). (a Cohen's d of .42 indicates a treatment effect (difference between control mean and intervention mean on the outcome measure) equal to 0.42 standard deviations (where standard deviation(SD) of interest if the SD of the outcome measure)

| Alpha | power | Effect size | N in each cell  (The allocation ratio = 1:1) | Total N |
| --- | --- | --- | --- | --- |
| 0.05 | 0.90 | 0.4 | 131 | 262 |
| 0.05 | 0.80 | 0.4 | 98 | 196 |

Thus, if we randomize 131 in the intervention group and control group for a total of 262 randomized, we will have 90% power to detect a treatment effect assuming that this difference is equal to .40 standard deviations. However, these calculations ignore dropout. We expect that 75% will complete our six-month follow-up, resulting in 98 respondents in the intervention group and control group at six-month. In this situation, we will have 90% power to detect an effect size equal to .47 SD, which is exactly equal to our best estimate of what effect we expect to see at month 4 in this trial.

## 3.3. Recruitment of participants

The company representatives and/or the principal investigator will visit study sites and meet with the employees, if possible in small groups, to explain the purpose and rough procedures of the study to increase interest for this program beforehand.

CRC will send out invitation mail to 1700 employees, of whom 680 will give the informed consent, of whom 272 will be candidates (K6>=5), of whom 245 will be eligible. These 245 will be randomized to intervention group (n=122) or to control group (n=123). They will be allowed to complete the six lessons within 10 weeks after the baseline survey. Those on the control group can receive the iCBT only after six-months.

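### Section 3.2 computes power on 262 randomised but section 3.3 plans 245, and the 90% power claimed after dropout rests on an unsourced 0.47 SD effect at an unscheduled month 4

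*Protocol*

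**What the plan says.** Protocol section 3.2 (Sample size assumptions and estimates) cites a systematic review of psychological treatments for subthreshold depression with a "d of 0.42 (95%CI: 0.23 to 0.60) at post-test". Its table then uses an effect size of 0.4 and has two rows (alpha, power, effect size, N per cell, total N): "0.05 | 0.90 | 0.4 | 131 | 262" and "0.05 | 0.80 | 0.4 | 98 | 196".

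The text adopts the first row: "if we randomize 131 in the intervention group and control group for a total of 262 randomized, we will have 90% power" at 0.40 SD. It says that this ignores dropout and expects 75% to complete six months, leaving 98 per arm. For those 98 per arm it claims "90% power to detect an effect size equal to .47 SD, which is exactly equal to our best estimate" of the effect at month 4.

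Section 3.3 (Recruitment of participants) gives a funnel of 1700 invited, 680 consenting, 272 with K6 of 5 or more, and 245 eligible. It ends: "These 245 will be randomized to intervention group (n=122) or to control group (n=123").

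Sections 5.1, 5.3.2 and 6.1.4 place the outcome surveys at three and six months after randomisation. No section schedules an assessment at month 4.

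**The concern.** Two statements in the protocol do not fit together.

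- **Two randomised totals.** The power statement needs 262, and the recruitment plan expects 245. The funnel counts only workers with K6 of 5 or more, which is the inclusion criterion and the population of the primary question. Workers with K6 of 4 or less form a separate stratum for a sub-analysis and do not make up the 17.
- **An effect size without a source.** The 90% power after dropout is attached to 0.47 SD. That value appears nowhere else in the protocol. It differs from the 0.42 cited and the 0.40 tabulated in the same section, and it is tied to a time at which nothing is measured.

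A reader who takes section 3.2 at its word will believe that the trial has 90% power, after dropout, at the effect it expects. A null BDI-II result would then be read as stronger evidence against the programme than the design supports. The reader also cannot tell which sample size is intended.

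**Working it through.** **Inputs.** Alpha 0.05, effect size 0.40, target power 90% and 80%, 131 and 98 per arm, 75% completion, cited effect 0.42, claimed effect 0.47 (all section 3.2); 245 randomised as 122 and 123 (section 3.3). The protocol does not say whether alpha is one- or two-sided. Two-sided is used here because it reproduces the table; one-sided would give 108 and 78 per arm.

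**Step 1: reproduce the table.** Normal approximation, n per arm = 2(z₁₋α/₂ + z₁₋β)²/d².

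- 90%: 2(1.960 + 1.282)²/0.40² = 131.3, against 131 in the table.
- 80%: 2(1.960 + 0.842)²/0.40² = 98.1, against 98 in the table.

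Both agree apart from rounding down.

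**Step 2: reproduce the post-dropout claim.** 131 × 0.75 = 98.25, so 98 per arm. The effect detectable with 90% power is (1.960 + 1.282) × √(2/98) = 0.463 SD (0.465 with the noncentral t). At 0.47 SD, power is 90.6%. The claim is correct for 98 per arm at 0.47.

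**Step 3: apply the recruitment plan.** 1700 × 0.40 = 680; 680 × 0.40 = 272; 272 × 0.90 = 245. Then 245 × 0.75 = 183.75, about 184 completers or 92 per arm.

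**Step 4: power.** Unadjusted two-sample t-test, two-sided alpha 0.05, noncentrality d√(n/2). For example, 0.40 × √(92/2) = 2.713. The normal approximation is then Φ(2.713 − 1.960) = 77.4%, and the noncentral t gives 77.0%. Noncentral-t results:

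| Completers per arm | d = 0.40 | d = 0.42 | d = 0.47 | Effect at 90% power |
| --- | --- | --- | --- | --- |
| 131 (262 randomised, no dropout) | 89.7% | 92.3% | 96.6% | 0.40 |
| 98 (262 randomised, 75% retained) | 79.6% | 83.3% | 90.6% | 0.47 |
| 92 (245 randomised, 75% retained) | 77.0% | 80.9% | 88.7% | 0.48 |

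**Step 5: split the loss at d = 0.40.** Dropout takes power from 89.7% to 79.6%, about 10 points. The smaller randomised number takes it from 79.6% to 77.0%, about 3 points.

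**Step 6: look for support for 0.47 and month 4.** Section 3.2 gives 0.42 with its source and 0.40 in the table. The Background quotes 0.68 and 1.16 for CBT in workers. None of these is 0.47. Follow-up is at months three and six only.

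**The case against.** Much can be said for the protocol. Its arithmetic is sound: 131, 98, and 90% power at 0.47 with 98 per arm all reproduce. Section 3.2 says openly that the 262 calculation ignores dropout, prints the 80% row for 98 per arm, and never claims 90% at 0.40 after dropout. The 245 is a forecast from rounded rates, whereas 262 is stated conditionally. The value 0.47 lies inside the cited interval of 0.23 to 0.60. All of this stands, and it limits the point to an inconsistent sample size and an unsupported assumption. It does not reconcile 245 with 262. Nor does lying inside an interval around 0.42 make 0.47 the best estimate.

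A reader might infer more than the document supports:

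- **That the trial's true power is 77%.** That figure belongs to one analysis, the unadjusted completer t-test, at one of three effect sizes in the section. Section 6.1.4 also plans ANCOVA and a mixed model on all randomised subjects, which could have more power. The protocol gives no baseline-to-follow-up correlation from which to compute it, and stating adjusted power can be left to the SAP.
- **That 0.47 was worked back from the sample left after dropout.** It is close to the 0.465 that 98 per arm can detect, but the document does not show how it was chosen.
- **That the invitation pool is a second material contradiction.** Section 3.1.2 lists 290 workers in company A and "all workers who belonged to three selected departments (N=about 1,500") in company B, about 1,790 against 1700 in section 3.3. The 1,500 is approximate. The same funnel gives 1790 × 0.4 × 0.4 × (245/272) = 258, so little changes.

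**Conclusion.** The point holds as a contradiction in the randomised number and an unsupported effect size. With the 245 that section 3.3 plans, 90% post-dropout power is not reached at any of the three effect sizes in section 3.2: about 77% at 0.40, 81% at 0.42 and 89% at 0.47. If 262 were randomised, 90% would be reached only at the unsourced 0.47, with about 80% at 0.40 and 83% at 0.42.

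These figures assume two-sided alpha 0.05, 1:1 allocation, 75% completion in each arm and an unadjusted comparison of completers' BDI-II means. Dropout, which the protocol discloses, accounts for most of the shortfall. The power statement needs rewording; randomisation, outcomes and analysis are not affected.

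**What to change.** 1. Use one randomised number in sections 3.2 and 3.3. The document does not say whether 245 or 262 governs, so the authors must choose.
2. Restate post-dropout power for that number at 0.40 and 0.42 SD, labelled as an unadjusted completer t-test at two-sided alpha 0.05. If 245: about 92 per arm, 77% and 81%. If 262: 98 per arm, 80% and 83%.
3. Give a source for the 0.47 SD best estimate, or delete it.
4. Replace month 4 with a scheduled assessment time (three or six months).

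This is a change of wording and needs no extra participants. The cost is a less favourable stated power.

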### 3.3.1. Assessment of eligibility

We will sent an invitation e-mail to all workers who belongs to company A or three selected departments at the headquarter of company B. Assessment of eligibility will be checked at the baseline survey. We prepared a website which contained full explanation of the study. Before the baseline survey, participants were invited to read the explanation on the website, and asked to click an “agree” button to show their consent to participate in the study; then they proceeded to the baseline questionnaire page.

Those who were found to be currently in major depressive episode will be excluded from this trial but will be contacted by the CRC, so that they would be advised to see an industrial physician or an extra-mural specialist. The CRC would explain by e-mail that, according to all the data accumulated so far, the subject was judged to profit more by seeing a specialist in person than by this iCBT.

### 3.3.2. Baseline assessments

Eligibility assessments will be combined with baseline survey. The baseline survey will therefore consist of the following variables.

1. sex
2. age
3. occupational, educational and marital statuses.
4. K6 score past a month
5. BDI-II score past two weeks
6. Work engagement
7. Health and Productivity Questionnaire
   - Total hours worked for the past 4 weeks, Relative absenteeism for the past 4 weeks (% of the working hours absent), Relative presenteeism for the past 4 weeks
8. Current treatment for physical and/or mental conditions
9. Any sick leave in the three months
10. CIDI results for mood disorders

### 3.3.3. Informed consent

We prepared a website which contained full explanation of the study. Before the baseline survey, participants were invited to read the explanation on the website, and asked to click an “agree” button to show their consent to participate in the study; then they proceeded to the baseline questionnaire page.

Candidates will be informed that their participation is totally voluntary, that even after voluntarily participating they can withdraw from the intervention or from both the intervention and the assessment at any time without stating the reason, and that neither participation nor withdrawal will lead to any advantage or disadvantage at the company. Data of each participant will be handled with sequentially allocated numbers to keep the participant’s confidentiality and kept in a computer not connected to the Internet. It will be accessible to the CRC only.

### 3.3.4. Intervention allocation

We will randomize eligible subjects to intervention and control groups at a ratio of 1:1. Randomization will be stratified on two variables, namely depression severity at baseline (K6=<4 vs. >=5) and center (company A or company B). Assuming that subjects are recruited from 2 sites, there will be a total of 4 strata. The study statistician will prepare 4 lists of random assignments ahead of time, one for each of the 4 strata. Each list will be blocked to ensure that the ratio of intervention to control is exactly 1:1 at set intervals within each stratum. The statistician will send these lists to the research assistant who is not involved in any other aspects of the study and who will build a spreadsheet that enables concealed sequential allocation and will be responsible for keeping these lists in the safe place.

Before randomizing an individual, the CRC will make a final determination of whether or not the person is eligible to be in the randomized trial. For example, prior to randomization, we will exclude those who having major depressive episode in the past a month. Once the CRC determines the eligibility of the participant, she will enter his/her registration number and the stratification variables to the spreadsheet which will automatically generate the allocation according to the pre-determined random sequence. The entered variables cannot be undone in order to guarantee allocation concealment.

Those randomized to control group will be put on a waiting list and after six-month can receive the iCBT if they wish to do so.

One stratification factor is K6>=5 and K6<=4. The cutoff score for K6 selected based on a previous report, which suggested that 4/5 is the optimal cutoff point for K6 in terms of discriminating community residents and patients with mood and anxiety disorders ([Sakurai, Nishi, Kondo, Yanagida, & Kawakami, 2011](#_ENREF_30)).

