# 2. OBJECTIVES

## 2.1 Primary question

Our primary question is:

“Among workers with subthreshold depression, will an Internet-based CBT program consisting of cognitive restructuring, assertiveness training, and problem-solving techniques in addition to the standard Employee Assistance Program (EAP) outperform EAP alone, in terms of depression severity (measured with BDI-II) and the onset of major depressive episode (measured with the web-version of the Japanese WHO-CIDI 3.0) at the end of the follow-up survey?”

The primary outcome measures in this study will therefore be:

1. depression severity at three- and six -month post-randomization as measured by the BDI-II
2. the onset of MDE during the 6-month follow-up as measured by the web-version of the Japanese WHO-CIDI 3.0

These two primary outcomes will be used to decide whether or not the intervention was effective.

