## 2.3. Subgroup hypotheses

The effectiveness of the program may differ according to the initial severity of depression. We will therefore use as one stratification factor high/low subthreshold depression (i.e., participants who scored 5 or more for the K6) at baseline survey, and analyze the results according to these a priori defined subgroups (selective intervention effect), while a sub-analysis will be done for all subjects including those with K6 scores of 0-4, as well. We will also analyze the results according to whole sample (universal intervention effect).

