### 6.1.4. Analyses of Primary Outcomes

Our two primary outcomes are the BDI-II measure of depression severity and the web-version of the Japanese WHO-CIDI 3.0 measure of the onset of MDE. The BDI-II will be assessed at three- and six-month follow-ups. The Japanese WHO-CIDI 3.0 will be assessed at the six-month follow-up.

The BDI-II is continuous/ordinal variables so will compute the mean score at three- and six-month follow-ups in the two groups, control and intervention. The onset of MDE is discrete variable so will compute the number of incidence at three- and six-month follow-ups in the two groups, control and intervention.

We will first do unadjusted analyses to compare the means using a t-test. We will then do several adjusted analyses. First, ANCOVA or multiple logistic regression analyses will be used to compare the three- and six-month means or the number of incidence on the outcome adjusting for baseline differences on the outcome. We will also do adjusted analyses which control for additional baseline variables, including variables which differ significantly between the control and intervention groups and variables which are strong predictors of the outcome under analysis.

These analyses will be restricted to subjects who complete the three- and six-month follow-ups (all of the statistical methods described above drop from the analysis those with a missing value on the outcome). Since a true intent-to-treat analysis estimates treatment effects based on data from all randomized subjects, not just those who complete a given follow-up, we will also do some mixed-model hierarchical linear models (HLM), using a mixed-model random coefficient model to estimate treatment effects based on all subjects. Subjects are "random effects" with varying intercepts (baseline values) and vary slopes (rates of change from baseline to three- and six-month). The dataset is structured so that each person has up to three records: baseline, three- and six-month follow-ups.

Even subjects who complete only the baseline enter into the analysis and are taken into account when estimating the three- and six-month mean in each group. Such a model can be fit in standard statistical packages such as SPSS, SAS, and STATA.

If conclusions based on the respondent-only and the intent-to-treat analyses are different, we will report intent-to-treat results.

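### The protocol contradicts itself on whether workers with K6 of 4 or less are randomised, and its primary analysis section does not name the K6 population

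*Protocol*

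**What the plan says.** On who enters the trial:

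- Protocol section 3.1 describes the study population as workers with subthreshold depression. Inclusion criterion 4 in section 3.1.1 requires "K6 scores greater than or equal to 5 at screening". The same criterion then adds in brackets: "while a sub-analysis will be done for all subjects including those with K6 scores of 0-4, as well".
- Section 3.3 takes 1,700 invitations to 680 consents, "of whom 272 will be candidates (K6>=5), of whom 245 will be eligible". Those 245 are split 122 and 123 between the arms. No worker with K6 of 4 or less is counted.
- Section 3.3.4 states: "Randomization will be stratified on two variables, namely depression severity at baseline (K6=<4 vs. >=5) and center (company A or company B". It counts four strata and has one blocked list made for each.

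On who is analysed:

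- Section 2.1 opens the primary question with "Among workers with subthreshold depression, will an Internet-based CBT program".
- Section 2.3 stratifies on "high/low subthreshold depression (i.e., participants who scored 5 or more for the K6) at baseline survey" and treats the resulting groups as a priori subgroups. It calls the analysis that includes K6 0-4 a sub-analysis, then separately plans a whole-sample analysis of a universal effect.
- Section 3.2 takes its effect size from a review of treatments for subthreshold depression.
- Section 6.1.4 runs the first primary-outcome analyses in completers and adds a mixed model, justified as follows: "Since a true intent-to-treat analysis estimates treatment effects based on data from all randomized subjects". Neither analysis carries a K6 restriction. Where the two lead to different conclusions, the intent-to-treat result is reported.

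**The concern.** There are two linked defects.

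**Eligibility and allocation conflict.** A worker with K6 of 3 fails criterion 4, yet section 3.3.4 holds a list for that worker. If the criterion governs, two of the four lists stay empty and the low subgroup in section 2.3 has no members. If the lists govern, people outside the stated entry criterion are randomised and the figure of 245 is wrong. This matters in practice because the coordinator makes the final eligibility decision and, under section 3.3.4, an entry in the allocation spreadsheet cannot be undone.

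**The primary population does not reach the analysis section.** The question is asked in subthreshold depression, but the section that governs the primary analysis never says so. If low scorers are randomised and section 6.1.4 is followed as written, the primary estimate describes a different and much wider population. A selective and a universal result would both exist, and section 6.1.4 does not say which one decides whether the intervention worked.

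**Working it through.** **1. The protocol's own sample size.** With a two-sided 0.05 test (sidedness is not stated, so this is an assumption) and n per arm = 2(z₁₋α/₂ + z₁₋β)² / d²:

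- 90% power, d = 0.40: 2(1.960 + 1.282)² / 0.16 ≈ 131.3, against 131 in section 3.2.
- 80% power, d = 0.40: 2(1.960 + 0.842)² / 0.16 ≈ 98.1, against 98.

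Both reproduce. The d of 0.40 rests on a review in subthreshold depression, so the calculation belongs to K6 of 5 or more.

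**2. How many low scorers there could be.** From the funnel in section 3.3:

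- Consenting with K6 of 4 or less: 680 − 272 = 408, and 408/680 = 60.0%.
- Eligibility among K6 of 5 or more: 245/272 = 90.1%. The protocol gives no rate for low scorers, so a range is assumed.

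| Assumed eligibility, K6 ≤ 4 | Eligible, K6 ≤ 4 | Total randomised | Share with K6 ≤ 4 |
|---|---|---|---|
| Not randomised (section 3.3 as written) | 0 | 245 | 0% |
| 80% | 326 | 571 | 57.1% |
| 90.1% | 368 | about 612 | 60.0% |
| 100% | 408 | 653 | 62.5% |

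**3. What pooling could do to power (illustration only).** Assume d = 0.40 in K6 of 5 or more, an effect δ in K6 of 4 or less, the same SD in both, and the 40/60 mix. Then pooled d = 0.4 × 0.40 + 0.6 × δ, and power ≈ Φ(d√(n/2) − 1.960).

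- Pooled n per arm: about 306 with everyone analysed, or about 230 at the 75% retention in section 3.2.
- K6 of 5 or more alone: 122 per arm, or 91.5 at 75% retention.

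| Analysis set | d | Power, everyone analysed | Power, 75% retention |
|---|---|---|---|
| K6 ≥ 5 only | 0.40 | 87.8% | 77.2% |
| Pooled, δ = 0 | 0.16 | 50.8% | 40.3% |
| Pooled, δ = 0.1 | 0.22 | 77.7% | 65.5% |
| Pooled, δ = 0.2 | 0.28 | 93.4% | 85.1% |

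Pooling lowers power if low scorers benefit little. It raises power at δ = 0.2 because the pooled set is about two and a half times as large (612/245 = 2.5). What changes for every δ below 0.40 is the quantity estimated: 0.16 to 0.28 SD across these rows, instead of the 0.40 SD the trial was sized for.

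**The case against.** The strongest reply is that the intent is clear enough. Criterion 4 carries its own qualifier, so K6 of 5 or more can be read as the main population, with low scorers randomised in their own strata for an extra analysis. On that reading all four lists are used and the low subgroup exists. Sections 2.1, 3.1 and 3.2 are set in subthreshold depression, and sections 2.3 and 3.1.1 both call the all-subjects analysis a sub-analysis. Because allocation is blocked within K6 strata, the comparison in K6 of 5 or more stays valid whether or not low scorers are also randomised.

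Much of this stands. A reader might infer that the protocol plans a primary analysis in which 60% of participants lack subthreshold depression, or that the trial would have only 40% power. The documents do not support either inference. The reference to all randomised subjects in section 6.1.4 is contrasted with completers and concerns missing outcomes, not K6. The mixed model is an additional analysis that prevails only if conclusions differ. The 40% figure needs a zero effect in low scorers, which no section states.

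The reply does not remove the conflict. If low scorers are randomised, section 3.3 is wrong to count only 245. Section 2.3 treats the K6 strata as subgroups while also calling the analysis of all subjects a sub-analysis, and it closes with a whole-sample analysis of unstated rank. The list of purposes in section 1 sets the depression-severity aim in subthreshold workers but the major depressive episode aim, which is also a primary outcome, among workers generally. The section that governs the primary analysis settles none of this. It is a conflict between protocol sections on eligibility and primary population, not a detail left to a statistical analysis plan.

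**Conclusion.** The concern holds as a contradiction over who is randomised, and as a failure to carry the primary population into section 6.1.4. The weight of the protocol favours K6 of 5 or more as the primary population, so the mixed population is a literal reading of section 6.1.4 and not the evident plan.

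The two readings give 245 randomised with no low scorers, or about 571 to 653 randomised with 57% to 62.5% low scorers. The second range rests on an assumed 80% to 100% eligibility in that group. The power figures are illustrative only: they assume an effect in low scorers, an equal SD and a two-sided test, their direction reverses within the range shown, and they do not address the major depressive episode outcome. The firm consequence is that following sections 3.3.4 and 6.1.4 literally would randomise people who fail criterion 4 and estimate the effect in a population other than the one in the primary question.

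**What to change.** - In sections 3.1.1 and 3.3, state whether otherwise eligible consenting workers with K6 of 4 or less are randomised. If they are, give the expected number in each K6 stratum and correct the total.
- In section 6.1.4, restrict the primary analysis, both completer and intent-to-treat, to randomised participants with baseline K6 of 5 or more. This matches sections 2.1 and 3.2.
- In section 2.3, label the whole-sample analysis secondary.
- If workers with K6 of 4 or less are not to be randomised, delete their strata from section 3.3.4 and remove the whole-sample analysis instead.

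An arm-by-K6 interaction test would be a reasonable addition but is optional.

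The cost is protocol wording in four or five sections, and the whole-sample result gives up any confirmatory status. If low scorers are randomised, both analyses are kept and the stratified allocation needs no change.

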An innovative way to deliver CBT-based treatment widely is with a computerized CBT (CCBT) and via the Internet CCBT (iCBT). The CCBT and iCBT programs teach basic information and skills based on the same CBT principles as face-to-face CBT programs do, with a highly structured format comprising educational lessons, homework assignments, and supplementary resources ([Titov, Andrews, & Sachdev, 2010](#_ENREF_35)). Previous studies have shown a significant positive treatment effect of CCBT and iCBT programs on depression and anxiety in the clinical setting ([Andrews, Cuijpers, Craske, McEvoy, & Titov, 2010](#_ENREF_2)). An iCBT program is particularly beneficial with its high anonymity ([Gega, Marks, & Mataix-Cols, 2004](#_ENREF_12)) and high accessibility ([Spek et al., 2007](#_ENREF_33)).

However, no iCBT program is available that would target specifically the general working population, the effectiveness of which would be tested with an randomized controlled trial (RCT). In addition, no previous RCT investigated a beneficial effect of an iCBT program on reducing a risk of depressive disorder which was diagnosed according to standardized diagnostic criteria, such as the DSM-IV ([American Psychiatric Association., 2000](#_ENREF_1)).

The purpose of this randomized controlled study is as follows:

1. to develop a new six-week iCBT program for workers who has subthreshold depressive symptoms in Japan.
2. to examine the effects of the iCBT program on improving the symptoms of depression at three- and six-month follow-ups among workers who has subthreshold depressive symptoms in Japan.
3. to decrease the risk of DSM-IV major depressive episode (MDE) through the six-month follow-up among workers in Japan.
4. to examine the effects of the iCBT program on improving work engagement and work performance at three- and six-month follow-ups among workers in Japan.

The study will be a two-arm, parallel-group, TAU-controlled, non-blinded randomized study.

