# 4. INTERVENTIONS

## 4.1. Description and schedule

In order for the randomization and start of intervention to be as close as possible, CRC will endeavor to randomize the participant immediately after closing for application and send the e-mail about iCBT program course description as soon as possible.

Participants who will be allocated to the intervention group studied the new iCBT program called the Internet CBT program; Useful mental health solutions series for business. The program is a six-week web-based training course to provide stress management skills. This program is structured into six lessons, with one lesson given per week. Learning one lesson required about 30 minutes, including homework. This program can be used anywhere the Internet is available.

One of the unique features of the program is that the training is provided along with a Manga (Japanese comic) story of a psychologist and a client worker to facilitate the understanding of the participants. Several merits of using a comic story and comic characters in education have been acknowledged through research. First, these materials help motivate individuals, and high motivation is useful to keep participants in the program ([Hutchinson, 1949](#_ENREF_16)). Second, they facilitate easy learning. A program with text combined with comic stories would be easier for a learner to understand compared to a text-only program ([Hutchinson, 1949](#_ENREF_16); [Sones, 1944](#_ENREF_32)). Third, comic stories foster learners’ interest in the program ([Sones, 1944](#_ENREF_32)). These merits might be applicable to education in the workplace, because most Japanese people of working age are familiar with comics.

In terms of the CBT components of the program, included are self-monitoring skills, cognitive restructuring skills, assertiveness, problem-solving skills, and relaxation skills. At the end of each lesson, participants are asked to submit homework to facilitate their understanding, although it is voluntary. Participants who will submit their homework will receive feedback from trained staff (clinical psychologists).

Participants will be allowed to complete the six lessons within 10 weeks after the baseline survey. Participants will be reminded by e-mail to complete each lesson if they had not already done so. Reminders will be sent from the research office to the participants every Monday.

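### The CRC decides eligibility, enters participants one by one and sees each allocation, with no fixed order of entry, so irreversible entry alone cannot guarantee concealment

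*Protocol*

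**What the plan says.** Section 1 describes the design: "The study will be a two-arm, parallel-group, TAU-controlled, non-blinded randomized study". Section 3.3.4 sets the ratio ("We will randomize eligible subjects to intervention and control groups at a ratio of 1:1") and the stratification by K6 group and company ("Assuming that subjects are recruited from 2 sites, there will be a total of 4 strata"). On the lists it says: "Each list will be blocked to ensure that the ratio of intervention to control is exactly 1:1 at set intervals within each stratum".

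The same section divides the work. The statistician prepares the lists. A research assistant with no other part in the study keeps them and builds the allocation spreadsheet. Before each randomisation, "the CRC will make a final determination of whether or not the person is eligible". The CRC then types in the registration number and stratification variables, and the spreadsheet returns the arm. The section adds: "The entered variables cannot be undone in order to guarantee allocation concealment".

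Two other places matter. On participant data, section 3.3.3 says: "It will be accessible to the CRC only". On timing, section 4.1 says: "CRC will endeavor to randomize the participant immediately after closing for application", and the CRC then sends the course e-mail.

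**The concern.** Concealment means that whoever decides who enters, and when, cannot foresee the next arm. Hiding the list is one part of that. The other is that the next arm cannot be deduced from the arms already given. Blocked lists that return to balance leak information, because once one arm is ahead within a block the other becomes more likely and eventually certain.

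Here one person sees every allocation in every stratum, holds the baseline data (section 3.3.2 includes BDI-II, K6 and CIDI results) and decides who is entered next. Because randomisation starts after applications close, that person chooses from a complete pool. If the order of entry followed a guess about the coming arm, participants with a better or worse outlook could be steered towards one arm. The comparison would then start from groups that differ for reasons other than chance.

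**Working it through.** **Inputs.** From the protocol: 1:1 ratio, four strata, blocked lists (section 3.3.4) and 245 participants with K6 of 5 or more to be randomised (section 3.3). The protocol gives no figure for block length or predictability, so length *b* is an assumption and a range is shown.

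**The plan's own denominator.** The section 3.3 recruitment figures reproduce: 1,700 × 0.40 = 680; 680 × 0.40 = 272; 272 × 0.90 = 244.8, or 245 (122 + 123). This covers only the two strata with K6 of 5 or more. The lists also cover K6 of 4 or less, so the counts below illustrate part of the randomisation.

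**Constant block length, known to the observer.** Let h = b/2.

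- Share of allocations known with certainty: 1/(h + 1).
- Share guessed correctly by always naming the arm with more places left: [h + ½(2^b / C(b,h) − 1)] / b.

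By hand for b = 4: of the six arrangements, two leave the last two places certain and four leave only the last. The mean is (2×2 + 4×1)/6 = 1.333 per block, and 1.333/4 = 33.3%. The chances of a correct guess at the four places are 1/2, 2/3, 2/3 and 1, which sum to 2.833, and 2.833/4 = 70.8%.

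| b | Certain | Of 245 | Best guess correct |
|---|---|---|---|
| 4 | 33.3% | 82 | 70.8% |
| 6 | 25.0% | 61 | 68.3% |
| 8 | 20.0% | 49 | 66.6% |
| 10 | 16.7% | 41 | 65.3% |
| 20 | 9.1% | 22 | 61.7% |
| No blocking | 0% | 0 | 50% |

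**If the length must be worked out.** In a simulation of one stratum (4,000 runs), every shorter constant even length was ruled out after a median of 6, 8 or 12 allocations for b = 4, 6 or 8. In 90% of runs it took no more than 22, 28 or 36. Ruling out shorter lengths does not prove the true one, so the certain shares above are upper bounds.

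**If lengths vary at random.** In a simulation of 1,000 runs of 240 allocations, the observer knew the set of lengths but not the current one. The certain share was about 5% for lengths 4/6 and about 2% for 4/6/8. The best guess was right 69% and 68% of the time, which is no lower than with constant blocks of 6 or 8.

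**The stated safeguards against each route.**

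| Route | Is it stopped? |
|---|---|
| Reading the list in advance | Yes: held by an uninvolved assistant |
| Re-entering someone to get another arm | Yes: entries are irreversible |
| Inferring the next arm from earlier ones | No |
| Choosing whom to enter next | No: no order of entry is laid down |

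**The case against.** The strongest reply is that constant blocks are an inference. Intervals set in advance need not be equal, may differ between the four lists and need not be known to the CRC. Leaving block details out of a protocol is normal practice. This stands. A reader might infer that the protocol prescribes constant blocks and that many allocations are therefore predictable in fact, but the text does not establish either.

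Second, the room for bias is narrow. Consent is given on the website before the baseline survey, so it cannot be steered by a foreseen arm. The criteria in sections 3.1.1 and 3.1.2 are mostly questionnaire or web-CIDI results, and an eligible respondent wrongly left out could be found in the stored data. This also stands. A reader might infer that borderline eligibility calls would be bent, but no clearly judgement-based criterion appears. Order of entry is what remains. Section 3.3.4 does call the allocation sequential, and section 3.3.3 mentions sequential participant numbers, but neither says that entry must follow those numbers.

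Third, it is tempting to argue that self-reported, unblinded outcomes make concealment more important. Those features create reporting bias, which concealment does not reduce, so the point rests on selection alone.

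**Conclusion.** The point holds as a minor one. One person decides eligibility, enters participants singly, sees each arm and holds the pool and its baseline data, with no fixed order of entry. Irreversible entry does not close that gap, so the sentence claiming that it guarantees concealment says too much. The missing block length is not a fault.

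The size depends on facts not in the protocol. If the length is constant and known or worked out, at most 33%, 25% or 20% of allocations are certain for lengths 4, 6 or 8. If lengths vary, about 2 to 5% are certain. In either case the best guess is right about two times in three. A reader might take this as a sign that allocation was manipulated. The documents show an opportunity and nothing more.

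**What to change.** In section 3.3.4, state that after applications close the list of eligible participants is locked before any allocation is made. The existing research assistant or the statistician, and not the CRC, then randomises the locked list in one batch, in registration-number order within the four strata. The CRC can still judge eligibility, because no arm is known at that stage. Prediction then has no effect, whatever the block length.

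Reword the last claim so that concealment rests on the locked list and independent allocation, with irreversible entry kept as a supporting measure.

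The cost is small: the assistant or statistician must be available to run the batch at closing. No extra participants or staff are needed. Varying the block sizes alone is not an adequate substitute, since it removes most of the certainty but leaves best-guess accuracy at about 68 to 69%.
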